#### Primary outcome – procrastination tendencies

2.7.1

*The Irrational Procrastination Scale* (IPS) is used to assess procrastination tendencies by assessing the extent to which participants procrastinate (Steel, 2007, Steel, 2010). This scale contains nine items scored on a five-point Likert scale ranging from 1 (very seldom or not true to me) to 5 (very often true or true to me). An example of an item is “My life would be better if I did some activities or tasks earlier”. The total scores can range from 9 to 45, with a higher score indicating higher levels of procrastination. With a good internal consistency of α = 0.91 (Steel, 2010), test-retest reliability of *r* = 0.84 (Guilera et al., 2018; Rozental et al., 2014), the IPS has also shown good content, structural, and substantive validity (Shaw and Zhang, 2021).

#### Secondary outcomes

2.7.2

The secondary outcomes are symptoms of depression, stress, anxiety and quality of life.

*The Patient Health Questionnaire* (*PHQ-9*) is used as the measure of depression (Kroenke and Spitzer, 2002). This questionnaire consists of nine items that can be answered on a four-point Likert scale ranging from 0 (*not at all*) to 3 (*nearly every day*). The total scores can range from 0 to 27, reflecting the severity of depression. Therefore, the higher the score, the more severe the symptoms of depression. The PHQ-9 has been shown to have high sensitivity (0.71–0.84), specificity (0.90–0.97), internal consistency (Cronbach's α = 0.86–0.89), test-retest reliability (*r* = 0.84) and validity (Kroenke et al., 2010; Wittkampf et al., 2007).

*The Generalized Anxiety Disorder scale* (*GAD-7*) is used to measure symptoms of generalized anxiety (Spitzer et al., 2006). This 7-item scale reflects the principal features of GAD such as worrying too much, feeling nervous or on the edge about different things. All items are measured on a four-point Likert ranging from 0 (*not at all*) to 3 (*nearly every day*). The total scores can range from 0 to 21 with higher scores indicating more severe GAD symptoms. The GAD-7 is shown to have high sensitivity (0.89), specificity (0.82), internal consistency (Cronbach's α ≥ 0.85), test-retest reliability (*r* = 0.84), validity, and is recommended as a valid screening tool for assessing the severity of GAD in clinical practice and research (Spitzer et al., 2006; Löwe et al., 2008; Rutter and Brown, 2017).

*The perceived stress scale* (*PSS-10*) is used as a self-report measure of perceived stress (Cohen et al., 1983). It consists of ten items measured on a five-point Likert scale ranging from 0 (*never*) to 4 (*very often*) and it reflects the degree to which the individual had perceived life as unpredictable, uncontrollable, and overloading in the past month. The total scores range from 0 to 40 with a higher score indicating higher levels of perceived stress. The PSS-10 is shown to have high validity, internal consistency (Cronbach's α = 0.74–0.91) and test-retest reliability (*r* = 0.74–0.88) (Cohen et al., 1983; Lee, 2012).

*The Mental Health Quality of Life questionnaire* (*MHQoL*) is used to measure quality of life (van Krugten et al., 2022). It consists of 7 items covering the dimensions of self-image, independence, mood, daily activity, physical health, relationships and future. Each item is measured on a four-point Likert scale ranging from 0 (*very dissatisfied*) to 3 (*very satisfied*). The total scores can range from 0 to 21 with higher scores indicating better quality of life. The MHQoL has been shown to have good psychometric properties in terms of validity, test-retest reliability (*r* = 0.85) and internal consistency (Cronbach's α = 0.85) (van Krugten et al., 2022).

#### Moderators and covariates

2.7.3

Previous studies have indicated that internet-based interventions rarely have a universal effect on all participants (Ebert et al., 2013; Karyotaki et al., 2018; Reins et al., 2021). Based on this, several socio-demographic variables and other program related variables will be assessed as potential covariates and moderators.

*Sociodemographic information* specifically age, gender, ethnicity, marital status, and whether the participant is currently receiving any psychotherapy or medication will be assessed as potential covariates.

*The Client Satisfaction Questionnaire* (*CSQ-8*) (Larsen et al., 1979) is used to measure the effects of participants' satisfaction with the overall intervention on the treatment outcome. The scale consists of eight items on a four-point Likert scale ranging from 1 (*low satisfaction*) to 4 (*high satisfaction*). The total scores can range from 8 to 32, with higher scores indicating greater satisfaction. The CSQ-8 has shown high reliability and validity for web-based interventions (Boß et al., 2016).

A single additional item is used to measure the participants' satisfaction with the individual modules of the intervention. At the end of each module the participants respond to the question “How useful was this module?” on a scale from 0 to 100, with higher scores indicating greater satisfaction with the module.

*System Usability Scale* (*SUS-10*) (Brooke, 1996) is used to measure the effects of program usability on treatment outcomes. It consists of ten items on a five-point Likert scale from 1 (*strongly disagree*) to 5 (*strongly agree*). The total scores range from 0 to 100 with higher scores indicating higher usability. The SUS-10 has become the most widely used standardized questionnaire to assess perceived usability and has shown good psychometric properties (reliability and validity) (Lewis, 2018).

*Adherence*, defined as “the degree to which the user followed the program as it was designed” (Donkin et al., 2011) is measured by dividing the number of main modules completed by a participant at time of post-test by the total number of main modules in the program, and multiplying this by 100 (Etzelmueller et al., 2020). The resulting percentage will indicate completion rate, with a higher value signifying greater treatment adherence.

*The Working Alliance Inventory for guided internet interventions* (*WAI—I*) (Gómez Penedo et al., 2020) is used to evaluate the effects of participant's satisfaction with the e-coach on treatment outcomes. The WAI-I consists of twelve items on a five-point Likert scale with a total score ranging from 12 to 60, where higher scores indicate higher satisfaction. The psychometric characteristics of the WAI-I yielded adequate results (Gómez Penedo et al., 2020).

### Sample size estimation

2.8

The power calculation is based on head-to-head comparison of the guided web-based intervention versus the waiting list (*t*-test). We anticipate a conservative estimate of Cohen's d = 0.50 based on a recent meta-analysis of randomized controlled trials that indicated an effect size of 0.55 for cognitive behavioral treatments for procrastination (Rozental et al., 2018b). Thus, if we set the statistical power at 0.8 and alpha at 0.05, according to two tails hypothesis, we need 63 participants per group (total *n* = 126) to detect an effect size of Cohen's d = 0.50. Previous literature has shown that guided web-based interventions have a dropout rate of 28 % (Richards and Richardson, 2012). Thus, considering the potential dropouts, the minimum required sample for the RCT is 176 participants with a target of 88 participants in each arm.

### Data analyses

2.9

Data on the primary endpoints and the majority of data on the secondary endpoints are continuous. All randomized participants will be included in the analyses based on the intent to treat principle (ITT). Missing values will be imputed using multiple imputations. In addition, we will conduct per protocol analysis, including only those who completed post-treatment and follow-up assessments. All analyses will be conducted using SPSS 26.

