#### Exploratory analyses – covariates and moderators

2.9.3

Descriptive statistics will be used to describe the socio-demographic characteristics of the participants in terms of age, gender, ethnicity, marital status, and whether the participant is currently receiving any psychotherapy or medication. Descriptive statistics will also be used for data exploration on the outcomes of the CSQ-8, SUS, WAI-I and adherence. Additionally, these outcomes will be tested as predictors and moderators or treatment outcome. The moderation analyses will be conducted using PROCESS macro for SPSS version 3.4. The macro provides bias-corrected 95 % confidence intervals (CI) for the indices using a bootstrap calculation based on 5000 samples (Hayes, 2017).

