The study's results should be considered in light of the following limitation. First, it should be noted that participation in the trial was completely voluntary. Therefore, it could be possible that participants differed from non-participants on important characteristics such as pretreatment motivation and help seeking behaviors that are known to influence treatment outcomes (Patterson et al., 2019; Sansfaçon et al., 2020). Additionally, it could be possible that severe procrastinators “put off” their participation long enough to miss out on treatment entirely. Nevertheless, our study was adequately powered to address the research question and the participants are likely to be a good representation of students that are open to e-health interventions. Second, given the nature of procrastination, it is possible that the study could encounter several dropouts and treatment adherence issues (Rozental et al., 2015a). Therefore, participants will receive support from e-coaches to increase motivation and adherence. Third, while the comparison with an inactive control precisely distinguishes the impact of the intervention, it can also overestimate the effects of treatment (Furukawa et al., 2014). In this study, participants in both groups will have access to treatment-as-usual options. Therefore, the results can be attributed to the actual effectiveness of the program. Fourth, we will not be able to make long-term comparisons between treatment and WLC as the control group will have access to the program four weeks post-randomization. However, the 6-month follow-up will allow a long-term within-group comparison for sustained treatment effectiveness. Finally, we use self-report measures that reflect the self-assessments of actual behaviors but could also be contaminated by other factors such as willingness to report difficulties and overestimating difficulties (Steel et al., 2001). Moreover, we use a non-validated single-item measure to assess participants' satisfaction with each module. However, previous studies have demonstrated that single-item measures can be practical alternatives to multi-item scales (van Hooft, 2014).

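### The 'per protocol' set is defined by returned questionnaires rather than treatment received, and on its plain reading it drops valid 4-week scores for a missed 6-month form

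*Protocol article*

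**What the plan says.** Section 2.9 (Data analyses) keeps all randomized participants in the main analysis and states "Missing values will be imputed using multiple imputations". It then adds: "we will conduct per protocol analysis, including only those who completed post-treatment and follow-up assessments". That is the whole definition of the set.

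Section 2.7.3 defines adherence as "the degree to which the user followed the program as it was designed" and measures it by "dividing the number of main modules completed by a participant at time of post-test by the total number of main modules", expressed as a percentage. Section 2.9.3 uses this measure only in exploratory work. Of the CSQ-8, SUS, WAI-I and adherence it says "these outcomes will be tested as predictors and moderators or treatment outcome".

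Section 2.9.1 takes the post-treatment IPS score as the dependent variable for the comparison between arms. Table 1 places that assessment 4 weeks after baseline and the follow-up at 6 months. Section 2.6 withholds the intervention from the waitlist for 4 weeks only. The Discussion accepts that no long-term comparison between arms will be possible.

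**The concern.** A per-protocol analysis is normally read as the effect in participants who were treated as planned. This set selects on answering questionnaires, which is different behavior. The label matters here because the Discussion itself warns: "given the nature of procrastination, it is possible that the study could encounter several dropouts and treatment adherence issues". A reader who wants to know what the program does for those who work through it will look to the per-protocol result, and this set cannot answer that question.

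The second difficulty is the 6-month condition. The only randomized contrast is at 4 weeks. Making inclusion depend on a form due about five months later selects participants on behavior that follows randomization and, for the waitlist, follows access to the program. It also discards 4-week scores that were validly collected.

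**Working it through.** **Who is in the set.** The rule in section 2.9, set against the adherence measure in section 2.7.3, for an intervention-arm participant:

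| Main modules completed | Post-test form | 6-month form | Adherence (2.7.3) | In the set (2.9) |
|---|---|---|---|---|
| 0 of 5 | returned | returned | 0% | yes |
| 5 of 5 | returned | missed | 100% | no |

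Membership does not depend on adherence at all. The second row also shows a valid 4-week score being discarded.

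**The plan's own figures.** Inputs from section 2.8: d = 0.50, two-sided alpha 0.05, power 0.80, dropout 28%.

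- Per arm, normal approximation: n = 2(1.960 + 0.842)² / 0.50² = 62.8, so 63, or 126 in total. This matches the article. (The t-based solution is 63.8, a trivial difference.)
- Inflation for dropout: 63 / 0.72 = 87.5, so 88 per arm and 176 in total. This also matches.

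**Illustration of the 6-month condition.** Two assumptions are needed that the documents do not supply: that 126 participants (63 per arm) have a 4-week score, and that a share e of them miss the 6-month form. The number remaining per arm is 63(1 − e). Power is that of a two-sided two-sample t-test at d = 0.50.

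| e (assumed) | Per arm | Total | Power |
|---|---|---|---|
| 0 | 63.0 | 126 | 0.80 |
| 10% | 56.7 | 113 | 0.75 |
| 20% | 50.4 | 101 | 0.70 |
| 30% | 44.1 | 88 | 0.64 |
| 40% | 37.8 | 76 | 0.57 |

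The normal approximation gives values about 0.01 higher in each row. The calculation shows lost precision only. It does not address the selection that the rule introduces, which has no size that can be worked out from the documents.

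**The case against.** Several points can fairly be made for the plan.

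- **The analysis is supplementary.** The main analysis keeps everyone, so no 4-week data are lost to the primary result. This stands and limits the weight of the point.
- **The article states how the set is built,** so an attentive reader is not misled. This is true, but the label still promises something the definition does not deliver.
- **Adherence is examined elsewhere,** as a predictor and moderator in section 2.9.3. This is also true, but that exploratory analysis does not make the per-protocol set an adherent set.
- **The wording may mean completers at each time point separately.** Section 2.9.1 uses the same pair of terms to list the time points analysed. This reading is possible but is not the plain one. If it is intended, the text should say so.
- **The 28% dropout is tied to no time point.** If it already covers loss up to 6 months, about 126 would remain in the set and the shortfall against the planned number disappears. This stands, and it is why the power figures are only an illustration.

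A reader might go further and infer that the imputation is left without any test of its missing-data assumption. The documents do not support that as a finding. The article does not name a missing-at-random assumption, and imputation details and sensitivity analyses may sit in a full protocol or analysis plan that is not shown.

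**Conclusion.** The point holds for the definition that the article states. The set is a questionnaire-completer set under a per-protocol label, and it takes no account of the adherence measure the trial already collects. On the plain reading of its wording, it also conditions the 4-week randomized comparison on a 6-month return.

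The consequence is confined to this one supplementary analysis. It would be wrong to infer that the primary intention-to-treat result is biased or underpowered because of it. The number of participants lost cannot be derived from the documents. The fall in power from about 0.80 to 0.75–0.57 depends on 126 participants having 4-week data and on an assumed further loss of 10–40%. The mislabelling does not depend on either assumption.

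**What to change.** 1. Rename the current set 'complete-case', and for the 4-week contrast require only the 4-week IPS score (with the baseline score used for adjustment). Keep the 6-month requirement only for analyses that use 6-month data.
2. If a per-protocol analysis is kept, define it in the intervention arm by a prespecified share of main modules completed by post-test. The trial team should set that share with the advised pace in view: section 2.5 advises one module per week for five main modules, while the post-test falls at 4 weeks, so someone on schedule need not have finished all five. Report the result as a non-randomized supplementary estimate, because the restriction applies to one arm only.

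The cost is a change of wording and a small additional analysis on data already collected. The downside is that the adherence-based estimate will be less precise and open to selection, since those who complete more modules may differ from those who do not.

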#### Primary outcome

2.9.1

Change in procrastination scores on the IPS will be assessed at post-treatment and follow-up assessments using multilevel mixed models linear regression with a restricted maximum likelihood algorithm for normally distributed data. Binomial models will be used for skewed data. The post-treatment score will be used as the dependent variable and trial arm condition (web-based transdiagnostic intervention vs WL) as independent while adjusting for baseline IPS scores. We will calculate the effect size of Cohen's d by subtracting the intervention group's average score on IPS measures from the average scores of the control group at the post- treatment and dividing the results by the pooled standard deviations. In addition, we will calculate the means and standard deviations of the groups at all time points. Analogously, the Cohen's d will be calculated for the difference score between the post-test measurement (t3 for the intervention group and t4 for the wait list group) and follow-up assessment (6 months, t5).

The reliability change index (RCI) will determine clinically significant change (Jacobson and Truax, 1991). The RCI will be calculated using the standard deviations at baseline and the test-retest reliability coefficient of the IPS (Guilera et al., 2018; Rozental et al., 2014). Participants will be classified as improved, deteriorated or no change based on the RCI for pretest and posttest measures.

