#### Secondary outcomes

2.9.2

For quality of life (MHQoL), depressive symptoms (PHQ-9), symptoms of anxiety (GAD-7) and stress-related symptoms (PSS-10), we will follow the same statistical approach described above for the IPS (with means, standard deviations and Cohen's d). Effects of the intervention on depression and anxiety will be analyzed separately for students scoring above the PHQ-9 (10 or more points) and GAD-7 (10 or more points) at baseline.

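### Skewness is no reason to analyse the IPS or the secondary sum scores with a binomial model; the fallback should be deleted and the linear model kept

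*Protocol article*

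**What the plan says.** Section 2.9.1 analyses change in IPS "using multilevel mixed models linear regression with a restricted maximum likelihood algorithm for normally distributed data", and then states: "Binomial models will be used for skewed data". On the outcome it says: "The post-treatment score will be used as the dependent variable", with trial arm as the independent variable and adjustment for baseline IPS. Cohen's d is to be computed from the two group means and the pooled SD.

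Section 2.9 describes the outcome type: "Data on the primary endpoints and the majority of data on the secondary endpoints are continuous". Section 2.7.1 describes the scale: "This scale contains nine items scored on a five-point Likert scale", and "The total scores can range from 9 to 45". It reports "good internal consistency of α = 0.91" and a test-retest correlation of 0.84.

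For the four secondary scales, section 2.9.2 says "we will follow the same statistical approach described above for the IPS". Section 2.8 bases the sample size on a two-sided t-test at d = 0.50.

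**The concern.** A binomial model describes a binary outcome or a count of independent successes out of a fixed number of trials. An IPS total is neither. Its items are strongly correlated, so its variance has no reason to equal the binomial variance. Skewness of the scores does not change that, and the normality assumption of the linear model concerns residuals, not raw scores.

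Two direct ways of carrying out the rule both do harm. Treating the total as successes out of 36 fixes the variance at a value that is probably too small, so standard errors are too small and false positives too frequent. Cutting the score into responder and non-responder makes a binomial model legitimate but discards information and power.

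Either way the primary test would concern an odds ratio, whereas the power calculation and the reported Cohen's d concern a difference in means. The rule covers the primary endpoint and all four secondary scales. It is a stated method that does not fit the outcome, not a missing detail.

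**Working it through.** **The plan's own figure.** Per arm, n = 2(1.96 + 0.842)²/0.50² = 62.8, so 63. An exact t-test needs 64 and has power 0.795 at 63. With 28% dropout, 63/0.72 = 87.5, so 88 per arm and 176 in total. The stated sample size reproduces, and it rests on a comparison of means.

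**Reading 1: the total as binomial out of 36.** From section 2.7.1 the score runs from 9 to 45, so 36 points lie above the floor. Set p = (mean − 9)/36; the binomial SD is √(36p(1 − p)).

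| Mean | p | Binomial variance | Binomial SD |
|---|---|---|---|
| 27 | 0.500 | 9.00 | 3.00 |
| 30 | 0.583 | 8.75 | 2.96 |
| 33 | 0.667 | 8.00 | 2.83 |

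The article gives no IPS SD or post-test mean. Assume means of 27 to 33 and an SD of 5 to 8. With r the baseline-to-post-test correlation (r = 0 for no adjustment), the dispersion is φ = SD²(1 − r²)/binomial variance. The actual two-sided error of a nominal 5% test is 2[1 − Φ(1.96/√φ)].

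| r | SD 5, mean 27 | SD 8, mean 33 |
|---|---|---|
| 0 (unadjusted) | φ = 25/9 = 2.78; 24% | φ = 64/8 = 8.0; 49% |
| 0.5 (assumed) | φ = 18.75/9 = 2.08; 17% | φ = 48/8 = 6.0; 42% |
| 0.84 (retest value, section 2.7.1) | φ = 7.36/9 = 0.82; 3% | φ = 18.84/8 = 2.36; 20% |

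These error rates do not depend on the sample size.

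**Cross-check from the reported alpha.** With nine items and alpha 0.91, the mean inter-item correlation is 0.91/(9 − 8 × 0.91) = 0.53. If each item taken alone had binomial variance (an assumption), then φ = 1 + 8 × 0.53 = 5.2, for an error of about 39%. Multiplying by 1 − 0.84² = 0.294 gives φ = 1.54 and about 11%.

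**Null simulation (illustrative).** Each scenario had 1,500 trials with 63 per arm, entry at IPS 32 or above as in section 2.2, and assumed item thresholds and latent correlations of 0.60 to 0.92. Observed baseline-to-post-test correlations were 0.34 to 0.64, and post-test skewness was −0.5 to −0.6. The baseline-adjusted binomial model rejected in 25% to 45% of trials. The baseline-adjusted linear model, on the same skewed scores, rejected in 4% to 5%.

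**Reading 2: dichotomize.** Take a normal outcome shifted by d = 0.50 and cut so that 20%, 30% or 50% of controls respond. The intervention rate is Φ(Φ⁻¹(control rate) + 0.50). The last column applies 28% dropout.

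| Control vs intervention | Power at 63 per arm | Per arm for 80% | Total |
|---|---|---|---|
| 20% vs 37% | 0.55 | 115 | 320 |
| 30% vs 49% | 0.59 | 103 | 288 |
| 50% vs 69% | 0.59 | 102 | 284 |

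The planned total is 176.

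**The case against.** The sentence is a fallback; the default is a baseline-adjusted linear mixed model. It does not say which binomial model. A quasi-binomial or beta-binomial model with a fixed denominator can handle a bounded, overdispersed score, and the type I error figures would then not apply. This stands: a reader might infer that any binomial analysis of the IPS is invalid, and the article does not support that. The harm shown belongs to an ordinary binomial model or to dichotomization, and no dichotomization of the IPS is planned for the primary model. If a negative binomial was meant, these figures would not apply either, but that model suits an unbounded, right-skewed count rather than a scale capped at 45 in a sample entered at 32 or above.

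The size of the inflation is also uncertain. The plan adjusts for baseline, so the unadjusted 24–49% overstates it. At r = 0.84 it could be absent (3% at SD 5), though not at SD 8 (20%). So high a correlation is unlikely in a sample restricted to high baseline scores.

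Three further inferences go beyond the document:

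- **Open model choice.** A reader might infer that the primary model is left to be picked once outcomes are seen. The article gives no skewness criterion, but the SAP, which is not shown, may supply one.
- **Change of reported effect measure.** Cohen's d is computed from group means whatever the model. Only the model coefficient and its test would change.
- **Skew on the secondary scales.** Nothing in the article shows that these scales are more skewed than the IPS.

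A SAP could add a threshold or a dispersion term. It would still have to override the stated pairing of skewness with a binomial model.

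**Conclusion.** The concern holds in a limited form: the stated fallback does not fit a bounded sum of correlated items that the plan calls continuous, and skewness does not justify it. Under an ordinary binomial model, the 5% test would have a true error of about 17–42% with baseline adjustment at r = 0.5 (24–49% unadjusted). This rests on assumed SDs of 5 to 8 and means of 27 to 33. The inflation could be small or absent with r near 0.84 and a small SD, or with an overdispersion term. Under dichotomization, power at 63 per arm falls from about 80% to 55–59% for control responder rates of 20% to 50%. In both cases the primary test would no longer address the mean difference for which the trial is powered. The linear model needs no such rescue: it held its error rate in the simulation with moderately skewed scores.

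**What to change.** Delete the sentence on binomial models and the condition that limits the linear model to normally distributed data. State that the baseline-adjusted linear mixed model is the primary analysis of the IPS, and the analysis of the PHQ-9, GAD-7, PSS-10 and MHQoL totals, whatever their skewness, with robust or bootstrap standard errors. If reassurance about distribution is wanted, name a rank-based or ordinal analysis in advance, as a sensitivity analysis only.

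The cost is one line of wording. The sample size stays at 63 per arm before dropout and 176 in total, and no additional data are needed.

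### Cohen's d is defined from post-treatment group averages although the primary model adjusts for baseline IPS, so d is less precise than the trial's own analysis allows

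*Protocol article*

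**What the plan says.** Section 2.9.1 (Primary outcome) of the protocol article specifies a mixed linear model: "The post-treatment score will be used as the dependent variable and trial arm condition" enters "as independent while adjusting for baseline IPS scores". So baseline IPS is in the primary test.

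The same section then gives an explicit recipe for the effect size at post-treatment: "subtracting the intervention group's average score on IPS measures from the average scores of the control group", then "dividing the results by the pooled standard deviations". Baseline is not mentioned in this recipe. The section also promises group means and SDs at every time point.

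No other standardised between-arm effect is defined. A further d, for change from post-test to six months, is described, but the Discussion treats that follow-up as a within-group comparison.

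Section 2.9.2 applies the same approach, naming Cohen's d, to MHQoL, PHQ-9, GAD-7 and PSS-10. Section 2.4 stratifies randomisation for site and gender, not for baseline IPS. Section 2.9 plans an intent-to-treat analysis with multiple imputation.

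**The concern.** The covariate is used for the test and left out of the effect size. When baseline and post-test scores are positively correlated, an unadjusted difference in means carries variance that the baseline-adjusted difference removes. It also carries part of whatever baseline difference arose by chance. With no stratification on baseline IPS, such a difference is possible in any single trial.

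What is at stake is the precision of the reported magnitude, not the validity of the test. The article states a formula here, so this is a method that has been fixed and not a detail left to an analysis plan.

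**Working it through.** **Inputs from the article.** Section 2.8: "We anticipate a conservative estimate of Cohen's d = 0.50"; "if we set the statistical power at 0.8 and alpha at 0.05, according to two tails hypothesis"; 63 per group; 28% dropout; 88 per arm. Section 2.7.1: IPS test-retest reliability 0.84. Section 2.2: entry requires an IPS of at least 32, on a scale of 9 to 45.

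**Assumed.** The baseline to post-test correlation r is not given. I take 0.3 to 0.6. The retest reliability of 0.84 is a rough ceiling.

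**Step 1: reproduce the plan's own figure.** Normal approximation: n per arm = 2 × (1.960 + 0.842)² / 0.50² = 62.8, so 63. Dropout: 63 / 0.72 = 87.5, so 88 per arm and 176 in total. Both match. (The exact t-test needs 63.8; power at 63 is 0.795.) This calculation is for an unadjusted comparison.

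**Step 2: SE of d with and without baseline.** In SD units and on the same pooled post-test SD:

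- unadjusted SE = √(2/n): 0.178 at n = 63 and 0.151 at n = 88;
- adjusted SE = √(2/n) × √(1 − r²).

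**Step 3: shift from chance imbalance.** The unadjusted d moves by r × (standardised baseline difference). One SE of that difference at 88 per arm is √(2/88) = 0.151 SD.

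| r | adjusted SE, 63 per arm | reduction in SE | adjusted SE, 88 per arm | shift in unadjusted d, one-SE imbalance at 88 |
|---|---|---|---|---|
| 0.3 | 0.170 | 5% | 0.144 | 0.05 |
| 0.5 | 0.154 | 13% | 0.131 | 0.08 |
| 0.6 | 0.143 | 20% | 0.121 | 0.09 |

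A two-SE imbalance doubles the shift, to 0.09 to 0.18 over r = 0.3 to 0.6. About 5% of trials would exceed two SE in either direction.

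**Step 4: simulation** (10,000 trials per setting, true d = 0.50). Both versions average 0.50, so neither is biased. At 63 per arm the unadjusted d correlates 0.29 (r = 0.3) or 0.49 (r = 0.5) with the baseline imbalance; the adjusted d correlates about 0. The two differ by more than 0.1 in 8% or 26% of trials at 63 per arm, and in 4% or 18% at 88.

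**Step 5: choice of denominator.** Dividing the adjusted difference by the residual SD would multiply d by 1/√(1 − r²). A d of 0.50 would become 0.50 / 0.954 = 0.52 at r = 0.3, or 0.50 / 0.80 = 0.63 at r = 0.6. The pooled unadjusted post-test SD keeps d on the scale that the article already uses.

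**The case against.** The strongest reply is that nothing here is wrong. The formula is a conventional Cohen's d. Under randomisation the unadjusted and adjusted differences estimate the same quantity. The test, its p-value and the adjusted mean difference already use the covariate. An unadjusted d also matches the t-test basis of the sample size and the meta-analytic 0.55 cited there, and the promised means and SDs at all time points let a reader see any imbalance. All of this stands, and it limits the point to precision. It does not remove it: the adjusted difference over the same pooled SD has the same target, and raw figures can stay in the table for comparability.

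The size may also be small. Entry at IPS of at least 32 restricts the baseline range, and Table 1 marks the IPS at screening (T0) but not at T1. Both tend to lower r. This stands too: for the IPS the gain is more likely near 5% than 20%. The secondary scales have no such cut-off in the full analysis, and their quoted retest reliabilities run from 0.74 to 0.88, so the gain there may be larger.

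Finally, the words used for group averages do not exclude model-estimated means. If those were intended, the proposed sentence simply makes it explicit.

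Three stronger readings are tempting and not supported. A reader might infer that d is biased, or that the primary result is in doubt; neither follows. A reader might infer that d is to be computed on observed data outside the imputation; Section 2.9 does not exempt it. And a reader might take d to be the trial's main reported result; the article does not give it that status.

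**Conclusion.** The point holds as a minor improvement. The plan defines its one standardised between-arm effect by a method that, on its natural reading, ignores a covariate already in the primary model. If r lies between 0.3 and 0.6, the cost is an SE of 0.178 where 0.170 to 0.143 was available at 63 per arm, and a shift in d of 0.05 to 0.09 for a one-SE baseline imbalance at 88 per arm. For the IPS the lower end of both ranges is more likely. The direction follows for any positive r; the size rests on an r that the article does not give. The unadjusted d remains unbiased, and the primary test and the sample size are unaffected.

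**What to change.** In Section 2.9.1, define the main d as the arm coefficient from the baseline-adjusted model, pooled over imputations, divided by the pooled unadjusted post-test SD (not the residual SD), with a 95% CI. Sign it so that a positive value favours the intervention, as the present formula does. In Section 2.9.2, apply the same definition to the four secondary outcomes, each with its own baseline score. Keep the raw means, SDs and raw d as labelled descriptives.

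The cost is a sentence or two of text. No new data, test or change in sample size is needed. The one drawback is that two d values appear in the table and must be clearly labelled.
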